### Intervention

#### Multicomponent training

According to the American College of Sports [10], for physical activity to be considered multicomponent training, it must contain at least three components. Components can be activities based on coordination of movement, balance, flexibility, cardiorespiratory capacity, muscle endurance, agility and cognition.

Therefore, our multicomponent training protocol was based on these recommendations, and will be performed in the following sequence: 1) a warm-up period, during which the individual must walk along a straight and flat track of 20 m for 5 min; 2) a cardiorespiratory capacity component where the individual should ride a stationary exercise bike for 20 min; 3) a lower limb strength training component, where the individual should sit and stand up from a chair without support for the upper limbs for 5 min; 4) a balance component, where the individual should walk 10 m along a path that will contain obstacles to deflect them (zigzag in cones) and another 10 m walk on unstable surfaces (carpets of different thickness) and up and down two steps; the individual will perform these components for 10 min; 5) an upper limb strength training, coordination, balance, and cognition component, where the individual should transfer three balls, weighing 1 kg each, from an upper shelf (at shoulder level) to a lower shelf (at pelvis waist level) and then to the floor, and then return the objects to the top shelf in the same sequence for 10 min; and 6) a flexibility and cooling-down component, where the individual will perform stretching in the standing position and relaxation in the sitting position for 5 min.

The sessions will be individualized, lasting 50 min, and in the 20-min period of training on the bike tDCS will be applied.

The Karvonen formula (220 – age) [27] will be used to determine the maximum heart rate of each participant, considering effort on a submaximum test of 60% to 80% of predicted heart rate. Before initiating training, the exercises will be demonstrated to familiarize the participants with the procedures. The treatment will be performed twice a week for 12 weeks (for a total of 24 sessions).

The following variables will be measured before, during (if necessary) and after each multicomponent training session as a protective measure against possible risks: heart rate, respiratory rate, blood pressure, oxygen saturation and lower limb fatigue level [28].

If the participants have any symptoms or signs that suggest a risk, the training will be stopped immediately. At the treatment site, there is a fire department rescuer who can be called for a medical emergency. All training sessions will be assisted and monitored by an experienced physiotherapist and two physiotherapy students positioned next to the participant.

#### Transcranial direct current stimulation

tDCS will be administered using the DC-STIMULATOR PLUS (NeuroConn) at 2 mA for 20 min during exercise bike training. Two nonmetallic electrodes will be used, wrapped in sponge previously moistened with saline solution. The anode electrode (5 × 5 cm) will be positioned over the left dorsolateral prefrontal cortex (F3) according to the International 10–20 Electroencephalogram System and the cathode electrode (5 × 7 cm) will be positioned supraorbital contralateral to the anode.

For sham tDCS, the electrode placement will be the same as the active protocol, but the stimulator equipment will only be turned on for the initial 30 s, following the parameters set for the stimulated mode device. Thus, participants will have an initial sense of stimulation but will not receive stimulation for the remainder of the 20 min. This is considered a valid form of control in studies with tDCS [29].

#### Determination of potential side effects

Possible adverse effects stemming from noninvasive brain stimulation will be determined using the tDCS Side Effects Questionnaire (translated into Portuguese) [30] after each session and immediately after the intervention.

**Fig. 1 Fig1:**
[figure not shown]
Schedule of enrollment, interventions, and assessments. 6MWT 6-min walk test, BESTest Balance Evaluation Systems Test, FIM Functional Independence Measure, GDS15 15-item Geriatric Depression Scale, Glittre-ADL Glittre Activities of Daily Living, MCT multicomponent training, tDCS Transcranial direct current stimulation, WHOQOL-bref World Health Organization Quality of Life Instrument

#### Sample size calculation

A pilot study was conducted with ten older adults separated into two groups (*n* = 5) to determine the number of participants we need to recruit. The sample size was calculated considering the primary outcome (functional capacity evaluated using the Glittre-ADL test), a significance level of α = 0.05 and 80% power, resulting in 22 participants to which 20% was added to compensate for possible dropouts. Thus, the sample will be composed of 28 participants, 14 in the intervention group (multicomponent training combined with active tDCS) and 14 in the control group (multicomponent training combined with sham tDCS). The calculation was performed using the G*POWER 3 software and repeated-measures analysis of variance (ANOVA) F test, considering the difference in the time required to complete the test in the pilot study (mean of 172.05 s in group 1 and 203.82 s in group 2, with a standard deviation of 30.79 s).

### Recruitment

Participants will be recruited from physiotherapy clinics at Nove de Julho University, Sao Paulo, Brazil.

To try and maintain participant retention until the end of the study, a weekly call routine will be created to remind participants and encourage them to continue participating through contact via WhatsApp or telephone calls.

### Allocation and blindness

The NeuroConn DC-STIMULATOR PLUS device has settings that allow one to select the active or sham protocol by codes consisting of a five-digit numeric sequence (provided by the manufacturer). There are 200 different possibilities (100 for each stimulus type of active or sham), so each participant will have their own code. Access to these numbers will only be provided for one of the researchers (researcher 1). This researcher will randomize the participants (http://www.randomization.com) and enter the codes according to the randomization (active group or sham) into the equipment, and thus it is not possible for the researcher who will apply the treatment and evaluate the results (researcher 2) to know the code and what is the treatment, ensuring blinding.

To ensure blinding of the participants and researcher 2 (a double-blind study) during stimulation, the device will appear switched on for both protocols (with no different external visual cues); however, for the active protocol the device will be programmed to operate for 20 min. For the sham protocol, the device will emit current for 20 s and then reduce this to zero (this programming is done by the manufacturer).

Researcher 2 will explain to the participant that they may feel a slight tingling that may continue or subside over time.

When treatment is over, researcher 1 will give researcher 2 a table for data analysis, with the names of participants divided into groups 1 and 2 (according to randomization), without treatment identification.

Researcher 2 will only know which group has received active and which group has received sham tDCS when the 30-day follow-up statistical analyses are complete.

To check blinding to treatment, a questionnaire will be delivered to each participant and researcher 2 at the end of each session asking whether the treatment was applied as active or sham tDCS.

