#### Assessment of functional capacity

To assess functional capacity, the Glitter-ADL test [31] will be used at three points (pretraining, post-training and 30 days after the end of training). T's an instrument validated for patients with chronic obstructive pulmonary disease, with acceptable reliability (95% CI −0.20 to −0.54).

The Glittre-ADL test is an instrument validated for patients with chronic obstructive pulmonary disease, with acceptable reliability (95% CI −0.20 to −0.54) [31], which has been previously tested in healthy older adults [38, 39], showing excellent intra-rater (ICC 0.90, 95% CI 0.86–0.93) and inter-rater (ICC 0.91, 95% CI 0.88–0.94) reliability (*P* < 0.001 for both). The intra-rater standard measurement error was 0.03 min and the inter-rater standard measurement error was 0.05 min. The minimal detectable change for intra-rater was 0.40 min and for inter-rater was 0.07 min.

The Glittre-ADL test consists of getting up from a chair with a backpack containing one weight (2.5 kg for women and 5.0 kg for men), walking 5 m on a flat track, going up and down steps measuring 17 cm in height and 27 cm in depth, and walking another 5 m to a set of three shelves, one at the top (at shoulder level), one in the middle (at pelvic waist level) and one at floor level. When reaching the shelves, the participant should transfer three balls, weighing 1 kg each, from the top to the middle and then to the bottom shelf and finally from the bottom shelf to the floor, and then return the balls in the same sequence until they reach the upper shelf. The task should be repeated in the reverse sequence until the participant is sitting again.

The complete test consists of five repetitions of this circuit, which should be performed as quickly as possible. Performance is given by the running time (in minutes) of the five laps with a shorter the time indicating better performance, considering a clinically important improvement between 7 and 40 s [38]. To be considered as preserved functional capacity, the test must be performed in approximately 2 min [39].

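### Researcher 2 both applies the stimulation and evaluates the results, so this person's blinding is at risk and not ensured as the protocol states

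*Protocol article*

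**What the plan says.** Under Allocation and blindness, the protocol article says of the device codes: "Access to these numbers will only be provided for one of the researchers (researcher 1"). Researcher 1 randomizes and enters the codes. From this the article concludes that "the researcher who will apply the treatment and evaluate the results (researcher 2") cannot learn either the code or the arm, and it presents blinding as secured.

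The same section adds that "the device will appear switched on for both protocols (with no different external visual cues"). Participants hear one explanation, that any tingling may persist or fade. Participants and researcher 2 each record a guess of the allocation after every session. Researcher 2 receives a list of names by group 1 and 2 once treatment has ended, and learns which group was active only after the 30-day analyses.

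Other sections bear on the point:

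- Transcranial direct current stimulation: "For sham tDCS, the electrode placement will be the same as the active protocol".
- Determination of potential side effects: the questionnaire is given "after each session and immediately after the intervention". The person who gives it is not named.
- Multicomponent training: every session is attended by "an experienced physiotherapist and two physiotherapy students positioned next to the participant". The text does not say whether researcher 2 is one of them.
- Assessment of functional capacity: the Glittre-ADL consists of five laps, "which should be performed as quickly as possible".

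**The concern.** Hiding the code closes one route to knowledge of the arm. A person who runs 24 sessions with a participant has others: what the participant says about sensation, and what side effects are reported. The protocol sends this information, or allows it to go, to the person who later evaluates the outcomes.

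The Glittre-ADL depends on effort, so an assessor who believes a participant had active stimulation could influence it without meaning to. Several secondary outcomes leave more to the examiner. Mini-BESTest items are graded 0 to 2 with assistance permitted, quadriceps strength is graded manually, and the Functional Independence Measure and quality of life are obtained by interview. If beliefs were mostly correct, a shift from this source would look like a tDCS effect, and the main comparison could not separate the two.

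**Working it through.** The point concerns who has which information, and the plan gives no figure to reproduce. The check sets the sections side by side.

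**1. Routes by which the arm could become known to researcher 2**

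| Route | What the protocol does | Closed? |
|---|---|---|
| Device code | Held and entered by researcher 1 only | Yes |
| Device appearance | No visible difference between arms | Yes |
| Electrode placement | Same in both arms, with brief current in sham | Yes |
| Participants' remarks on sensation | One neutral explanation for all | Weakened, not closed |
| Side-effects forms | Collected after each session, collector not named | Not addressed |
| Named group list | Given at the end of treatment | Not clearly closed before the 30-day test |

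Active current lasts 20 min. Sham current lasts 30 s in the stimulation section and 20 s in the allocation section, and these two passages must be reconciled. On either figure the arms differ greatly in length of current. The neutral explanation itself allows for sensation that lasts or fades. The documents do not say how often participants notice a difference.

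**2. Number of occasions**

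2 sessions per week × 12 weeks = 24 sessions per participant. 28 × 24 = 672 sessions, if nobody drops out or misses one. This counts occasions on which a cue could arise, not cues received. Researcher 2 is asked for a guess at each. The guess measures loss of blinding but does not prevent it, and it asks the evaluator to commit to a belief up to 24 times before the post-training test.

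**3. Timing of the group list**

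- If treatment being over refers to the individual participant, the list always precedes that participant's 30-day test.
- If it refers to the whole trial, take the Trial status dates and assume training starts at recruitment. The last participant, recruited on 30 July 2019, ends 12 weeks (84 days) later on 22 October and has the 30-day test on 21 November. A list released on 22 October precedes the 30-day test of anyone whose training ended after 22 September, that is, anyone recruited after about 30 June.

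With only two groups, a correct belief about one participant, or about which group improved more, would label everyone on the list.

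**4. A yardstick, not an estimate of bias**

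The pilot difference is 203.82 − 172.05 = 31.77 s. The lower end of the range the article calls clinically important is 7 s, and 7 / 31.77 = 22% of that difference. The quoted inter-rater measurement error is 0.05 min × 60 = 3 s. It describes random disagreement between raters and does not bound a systematic shift.

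**The case against.** The strongest reply is that a dual role does not unblind anyone. The protocol does more than hide a code: it matches appearance and montage, gives a brief sham current, uses one script, and withholds treatment identity until the 30-day analyses are complete. It also tests the risk directly with a guess after every session. The group list is described as being for data analysis, so it may well be meant for after follow-up. No section says who times the Glittre-ADL, who collects the side-effects forms, or that reports differ by arm.

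Most of this stands. A reader might infer that the assessor is in effect unblinded, or that the result will be biased towards active tDCS. The documents support neither. They show open routes, not that information passed along them, and any bias favours active tDCS only if beliefs are mostly right. That researcher 2 times the primary outcome is an inference from the stated duty to evaluate results, although no other assessor is named. If that duty meant data analysis only, the article would name no outcome assessor, and its double-blind claim would cover only participants and researcher 2. The section would need correcting on that reading too.

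What does not stand is the article's own certainty. Its safeguards mask the device, and its guesses detect a failure after the event. Neither justifies saying that knowledge of the treatment is impossible.

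**Conclusion.** The point holds as a design weakness that should be corrected: the claim of ensured blinding is stronger than the procedure described, for the one person who both delivers treatment and evaluates outcomes. The size of any bias cannot be derived from the documents, and no figure is offered for it. The conclusion rests on two readings. Evaluating the results is taken to include the outcome assessments, and the end of treatment is taken literally as the time the group list is released. If the list is in practice held until follow-up is complete, that part falls away and the rest remains.

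**What to change.** Where researcher 2 is not the physiotherapist who attends the sessions:

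- Session staff already present, also blind to the code, place and remove the electrodes, collect the side-effects forms and complete the per-session operator guess.
- Researcher 2 performs only the pretraining, post-training and 30-day assessments, and sees no side-effects forms before the last of these.

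In every case:

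- Release the group 1 and 2 list only after all 30-day assessments are complete and the data are locked.
- Report the blinding guesses by arm, for participants and for the operator.
- Replace the statement that blinding is ensured with one that describes the procedure, and name the outcome assessor.

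The cost is a short amendment and a re-allocation of tasks. Researcher 2 can no longer cover sessions. Recruitment was already under way, so any change of assessor should apply to a participant's whole set of assessments and not fall between baseline and follow-up. If researcher 2 is the session physiotherapist, separating the roles may need an additional person, because the only other team members named either attend every session or hold the codes. The measures listed for every case need no extra staff.

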**Methods:**

Twenty-eight elderly people from the community will participate in the study, and will be randomized into two groups: 1) multicomponent training associated with active tDCS; and 2) multicomponent training associated with sham tDCS. The multicomponent training sessions will be held twice a week for 12 weeks, totaling 24 sessions. The tDCS will be administered over the dominant dorsolateral prefrontal cortex at the same time as multicomponent training, with an intensity of 2 mA, for 20 min. The evaluations will be made pretraining, after 24 training sessions and 30 days after the end of the training.

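### The masked analysis table labels the arms groups 1 and 2, which matches the order in which the abstract lists active and sham, and nothing says the labels are assigned independently of that order

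*Protocol article*

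**What the plan says.** Under Allocation and blindness, researcher 1 holds the device codes, randomises the participants and programs the stimulator. Researcher 2 applies the treatment and assesses the results. The handover is described as follows: "When treatment is over, researcher 1 will give researcher 2 a table for data analysis". The table is specified as "a table for data analysis, with the names of participants divided into groups 1 and 2 (according to randomization), without treatment identification". The intended end of masking is also stated: "Researcher 2 will only know which group has received active and which group has received sham tDCS" once the statistical analyses of the 30-day follow-up are finished.

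The Methods paragraph of the abstract says that participants will be "randomized into two groups: 1) multicomponent training associated with active tDCS; and 2) multicomponent training associated with sham tDCS".

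The Sample size calculation section uses the same two labels for the pilot, "mean of 172.05 s in group 1 and 203.82 s in group 2", without naming the treatment that either pilot group received.

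The Outcomes section places the last Glittre-ADL test 30 days after training ends.

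**The concern.** A two-label mask works only if the labels carry no information about the arms. The labels chosen here are the two numbers that the abstract attaches, in a list, to active and sham stimulation. Researcher 2 works under this protocol and could reasonably suppose that the table keeps its order.

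Three features of the plan make this worth closing off:

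- **The roles are combined.** The person who receives the table has treated the participants, assesses them and, by implication, analyses the data.
- **The table lists names.** A guess about the two labels becomes a guess about each individual whom researcher 2 knows.
- **Assessment may still be under way.** The Depression scale section says that all assessments are repeated at 30 days. Several depend on the assessor: graded mini-BESTest items, an interview-based FIM and manual muscle grading.

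The Data analysis section also leaves some judgement until the data are in hand: visual assessment of normality by treatment group, an imputation method matched to the pattern of missing data, and a later look at individual results. These are best made without a belief about which group is active.

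**Working it through.** No figure in the plan bears on this point, so the check is a comparison of the passages.

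1. **Labels on the table.** Allocation and blindness fixes them as groups 1 and 2, attached to names.
2. **Where else the numbers 1 and 2 are attached to the arms.** The abstract lists active first, as 1, and sham second, as 2. This is the only place where the randomised arms are numbered with their treatments.
3. **The pilot labels.** Sample size calculation gives "mean of 172.05 s in group 1 and 203.82 s in group 2, with a standard deviation of 30.79 s". The section names the intervention arm before the control arm, and group 1 has the shorter, hence better, time. That agrees with the abstract's order but does not prove it, because neither pilot group is tied to a treatment.
4. **Any statement that separates the table's labels from the published order.** There is none. The table is said to carry no treatment identification, which states the aim. The article does not describe how researcher 1 decides which arm becomes group 1.
5. **Who receives the table, and when.** Researcher 2 receives it when treatment is over. If this means each participant's own treatment, every 30-day assessment is still ahead. If it means the end of treatment for the whole trial, at least the last participants to finish still have theirs to come. No wait for the 30-day data is stated on either reading.
6. **What the labels could give away.** Two labels can be matched to two arms in 2 ways. Suppose researcher 2 assumes the abstract's order. The chance of being right is then:
   - 1/2 if the labels were assigned by a random draw;
   - 1 if the table copies the published order;
   - 0 if the order was deliberately reversed.

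   The article does not say which of these applies, so no single figure can be given. A stated random draw would fix it at 1/2.

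**The case against.** The strongest reply is that no code has been published. The abstract's numbers are list punctuation, and the article numbers the training components, the assessment occasions and the test tasks in the same style. Where the body describes the arms, under Sample size calculation, it calls them intervention and control, without numbers. The remark that the table is divided according to the randomisation most naturally means that participants are split by assigned arm. It does not say which arm is called 1. The section also states outright that treatment is not identified and that researcher 2 stays masked until the analyses end. A researcher 1 who copied the abstract's order would be working against that intention. Finally, a condensed article may leave the assignment of labels to a fuller document.

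Most of this stands. A reader might infer that researcher 2 can simply read the allocation off the list, and might cite the faster pilot group 1 in support. The documents do not support that inference. It needs a mapping that is stated nowhere, and using the pilot times as a clue presupposes the same mapping.

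The reply does not remove the narrower point. The article did not leave the labels to another document: it specified them, and it chose the pair that matches its own listing of the arms. An intention not to identify treatment does not prevent the inference.

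**Conclusion.** The point holds as a minor weakness in how the mask is specified. The labels coincide with the published order of the arms, they are attached to names, and they go to the person who treats, assesses and receives the data for analysis. Nothing is described that would defeat the obvious guess. The consequence is conditional: only if the table follows the published order could researcher 2 infer individual allocations before the 30-day assessments and analyses are finished. No unmasking is documented, and the article gives no basis for estimating any resulting bias in the Glittre-ADL time or other outcomes.

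The early handover is the firmer part, because it does not depend on the numbering. Names grouped by arm reach the assessor with no stated wait for the last visit. The two parts need to be closed together. Delaying the list alone would leave the mask at the analysis stage resting on these labels. Relabelling alone would leave the assessor holding a grouped list of names while visits are pending.

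**What to change.** Revise the handover sentences under Allocation and blindness in three respects:

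- **Labels.** Replace groups 1 and 2 with two neutral labels that appear nowhere else in the protocol, for example X and Y. Researcher 1 ties them to the arms by a random draw and holds the key until the 30-day analyses are final.
- **Identifiers.** List participants by study number instead of name.
- **Timing.** State that the list is released only after the 30-day data are complete and locked.

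The cost is a few words of protocol text and one random draw by researcher 1, with no extra staff, visits or data. Comparisons between groups could not start until the 30-day data are locked. The plan already keeps researcher 2 masked until the 30-day analyses are complete, so the delay is compatible with it.
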